### Participants

This trial will be conducted in primary and secondary midwifery care settings in Amsterdam and The Hague, The Netherlands. All study procedures and informed consent forms received approval from the Ethics Review Board of the Faculty of Social and Behavioural Sciences at the University of Amsterdam (certificate number 2013-CDE-3064). This trial is registered in the Dutch Trial Register (NTR) under number 4302. Participation is entirely voluntary and pregnant women and/or their partners can stop participating at any time without having to sign anything or provide a reason for stopping.

### Inclusion criteria

Participants are primiparous and multiparous women, aged ≥18, fluent in the Dutch or English language who are more than 16 weeks and less than 26 weeks pregnant at baseline, and are experiencing a high level of FoC (W-DEQ-A ≥66) [9]. If an eligible woman agrees to participate, her partner will be asked to take part in the study as well. As ‘partner’ we refer to the father or co-parent of the expected baby, or a significant other person related to the pregnant woman who will be present at the birth. Pregnant women may enter the study without a partner or a significant other.

### Exclusion criteria

Exclusion criteria for this study are: (a) previous acute psychotic episode or diagnosed psychotic disorder; (b) current suicidal risk; (c) current substance use and dependency; (d) borderline personality disorder in the pregnant woman or her partner; (e) current trauma unrelated to childbirth traumatic stress disorder; or (f) participation in a MBP within the past year. The use of antidepressant medication, as long as the prescribed dose remains stable during the study, participation in an on-going psychological intervention or a prenatal education course, or a childbirth trauma as assessed by the Traumatic Event Scale (TES-B) [58] are not exclusion criteria. Women with a multiple gestation, HIV infection, or at high risk for premature labour will be excluded. Please see Procedure section below for a description of a two-stage exclusion protocol that will be employed.

### Intervention: The Mindfulness-Based Childbirth and Parenting (MBCP) programme

The MBCP programme [40] developed in the United States by midwife and mindfulness teacher [name], CNM, MA, is a formal adaptation of MBSR specifically developed for the expectant parent population. The teachings of mindfulness through formal and informal meditations are fully integrated with the knowledge of the psychobiological processes in pregnancy, birth, breastfeeding, postpartum adjustment and the psychobiological needs of the infant. MBCP as developed by [name] includes nine weekly three-hour classes, a 7-hour day of silent meditation practice and a 3.5-hour reunion gathering after all the babies have been born. For purposes of this study, the standard MBCP was adapted (with permission by [name]). Two first classes were combined as Class 1 and the 7-hour day of silent meditation practice was reduced to one 3-hour class (see Table 2). Expectant parents are asked to commit to practicing the formal meditations at home for 30 min a day, six days a week with instructional CDs that are given as part of the course materials. Adherence to the intervention is assessed by reporting the number of classes attended and weekly diaries of the amount of time spent between sessions in formal daily meditation practice and being mindful of the activities of daily living (informal practices). The importance of keeping a meditation diary will be emphasized. Each MBCP course will be taught by an experienced midwife, who, in accordance with the MBCP protocol, has been trained as an MBCP teacher by [name]. All MBCP sessions will be video recorded to assure fidelity to the MBCP model. Ratings of fidelity to the MBCP model will be carried out by two independent raters. The MBCP sessions will be free of charge and take place at a Mindfulness Centre in Amsterdam and The Hague.

**Table 2 Tab2:** Outline of the Dutch Adaptation of the Mindfulness-Based Childbirth and Parenting Programme

Week 1	Background of mindfulness, the MBCP programme, introduction to mindfulness meditation through an eating meditation, awareness of breathing meditation.
Week 2	Body scan meditation, attitudinal foundations of mindfulness, community building.
Week 3	Awareness of breathing meditation, body scan meditation, psycho-education: physiology of childbirth from a body-mind perspective.
Week 4-6	Yoga, sitting meditation, pain meditations using ice and a variety of pain-coping strategies, expanding the capacity to “be with” unpleasant/challenging sensations in the body and unpleasant or stressful thoughts and emotions, 3-Minute Breathing Space meditation, exploration of the notion of “being in control” during childbirth, psycho-education: baby's journey through the pelvis.
Week 7	Session of silence, body scan, yoga, sitting meditation, mindful eating, walking meditation, mindful speaking and listening inquiry practice regarding fears and joys around childbirth and the life change the couple is living.
Week 8	Loving-kindness meditation, psychoeducation: biological, emotional and social needs of the newborn and mindfulness practice for moment to moment caretaking, the needs of the postpartum family.
Week 9	Psychoeducation: physiology of breastfeeding, mindfulness as a skill for coping with breastfeeding challenges and postpartum adjustment, closing ceremony.

### Active Comparison Condition: Fear of Childbirth Consultation (FoCC)

The target sample of pregnant women included in this study suffer from intense FoC. In order to acknowledge the fears of these women we have upgraded care as usual into structured consultations on FoC (FoCC). FoCC consists of an adaptation of the Biopsychosocial Model [5] and the Childbirth Plan of the Royal Dutch Organization of Midwives (KNOV) [59].

This individualized programme for expectant couples includes two consultation sessions with a trained midwife of one-hour each over a nine-week period (see Table 3). The aim of FoCC is to gain insight into the variety of specific factors playing a role in the origin and presence of fear and stress around pregnancy, birth and the postpartum period as well as designing a suitable coping plan based on the particular fears and stresses, and includes some components of psychoeducation about fear. A structured form is used to collect information about FoC related factors and for the coping plan. The coping plan may include referral to a psychologist or other mental health care services. All FoCC sessions will be audio recorded in order to assure treatment fidelity. Two recordings per consultation will be randomly selected and evaluated by an independent midwife. The free of charge FoCC sessions will take place at the participant’s midwifery practice or place of residence.

**Table 3 Tab3:** Outline of the Two Sessions of the Fear of Childbirth Consultations

FoCC First Consultation
Mapping of the bodily, mental and social factors underlying FoC and the postpartum period. Interview about the pregnant woman’s overall state of physical health and current pregnancy, her mental health and emotional state, her ideas and values regarding being pregnant, the process of giving birth and being a parent, incidence of psychopathology in her family of origin, her most severe fears about childbirth and the postpartum period, her relationship with her partner, family, presence of social support, workplace experiences, important life events and potential vulnerabilities. A written psychoeducation about FoC and matching behavior from a body and mind perspective is provided.
FoCC Second Consultation
Designing an Individual Childbirth Plan based on the findings from the first consultation and the pregnant woman’s wishes, including the care provider’s, partner’s and family’s attitudes towards her upcoming childbirth, the woman’s intrinsic coping strategies regarding childbirth including her approach to labour pain and 2nd stage pushing, potential requests for care and guidance from her care provider and family, her ability to adapt to possible medical interventions, and guidance regarding first contact with her newborn.

### Outcome measures

In this study several assessment tools will be used. Some measures were translated specifically for this study. Translations were made in accordance with the scientific standards for translating questionnaires [60] and permission to translate has been given by the original authors. Table 4 presents an overview of the primary and secondary outcome measures and the time points of study assessments.

**Table 4 Tab4:** Overview of Measures, Outcomes, and Corresponding Measurement Occasions for the (pregnant) Women and their Partners

Measure	Outcome domain	Measurement occasion			
		T1	T2	T3	T4
W-DEQ-A	Anticipated fear of childbirth	X	X		
W-DEQ-B	Experienced fear of childbirth			X	X
PDSS^a^	Perinatal disaster scenarios	X	X	X	X
PAFS	Responses to anxiety and fear	X	X	X	X
CLP	Catastrophizing of labour pain	X	X		
LPAQ	Acceptance of labour pain	X	X		
VAS	Labour pain intensity	X	X	X	
WAOI^a^	Willingness to accept interventions	X	X		
DASS-21^a^	Depression, anxiety and stress	X	X	X	X
PSS^a^	Stress	X	X	X	X
EPDS	Prenatal/postnatal depression	X	X	X	X
PES-US	Uplifting experience of pregnancy	X	X		
NPSI-SF^a^	Parenting stress			X	X
EQ-5D^a^	Quality of life	X	X	X	X
PSQI^a^	Sleep quality	X	X	X	X
HSDQ-I^a^	Insomnia	X	X	X	X
ISVIS^a^	Interpretation of infant sleep	X	X	X	X
BISQ	Infant sleep			X	X
MAF^a^	Fatigue	X	X	X	X
SIL^a^	Satisfaction with birth			X	X
MR	Medical report about perinatal period				X
BSES-SF	Breastfeeding self-efficacy			X	X
FFMQ^a^	Mindful awareness	X	X	X	X
IM-P^a^	Mindful parenting skills			X	X
SCS-SF^a^	Self-compassion	X	X	X	X
PHCQ	Costs in and outside the healthcare sector	X	X	X	X

*Note*. ^a^instruments are filled in by (pregnant) woman and partner, others are filled in by (pregnant) women only. T1 = pre-intervention; T2 = post-intervention; T3 = two -four weeks after birth; T4 = 16–20 weeks after birth. MBCP or FoCC takes place between T1 and T2. *BISQ* Brief Infant Sleep Questionnaire, *BSES-SF* Breastfeeding Self-Efficacy Scale-Short Form, *CLP* Catastrophizing Labour Pain, *DASS-21* Depression Anxiety Stress Scale, *EPDS* Edinburgh Prenatal/Postnatal Depression Scale, *EQ-5D* Five-Dimensional EuroQol, *FFMQ* Five Facets Mindfulness Questionnaire, *HSDQ-I* Holland Sleep Disorders Questionnaire-Insomnia subscale, *IM-P* Interpersonal Mindfulness in Parenting scale, *ISVIS* Infant Sleep Vignettes Interpretation Scale, *LPAQ* Labour Pain Acceptance Questionnaire, *MAF* Multidimensional Assessment of Fatigue, *MR* Medical Report, *NPSI-SF* Nijmeegse Parental Stress Index-Short Form, *PAFS* Perinatal Anxiety/Fear Scale, *PES-US* Pregnancy Experience Scale-Uplifts Subscale, *PDSS* Perinatal Disaster Scenarios Scale, *PHCQ* Perinatal Healthcare Costs Questionnaire, *PSQI* Pittsburgh Sleep Quality Index, *PSS* Perceived Stress Scale, *SCS-SF* Self Compassion Scale Short-Form, *SIL* Salomon’s Item List, *WAOI* Willingness to Accept Obstetrical Interventions, *W-DEQ-A* Wijma Delivery Expectancy Questionnaire-version A, *W-DEQ-B* Wijma Delivery Expectancy Questionnaire-version B

### Primary outcome measures

Primary outcome measures are (a) FoC, (b) labour pain, and (c) willingness to accept obstetrical interventions without medical indications.

The complexity of FoC will be measured by three instruments, namely the W-DEQ- A and B [3], the newly developed Perinatal Disaster Scenarios Scale (PDSS), ([name], [name], [name], [name]: PDSS, unpublished), and the experimental Perinatal Anxiety/Fear Scale (PAFS), ([name], [name], [name]: PAFS, unpublished). First, anticipated and experienced levels of FoC will be assessed with the 33 items self-report W-DEQ- A and B covering several domains of FoC: (a) general fear, (b) negative appraisal, (c) loneliness, (d) lack of self-efficacy, (e) lack of positive anticipation, and (f) concerns about the child [61]. Second, the individual perinatal fear-eliciting beliefs, in pregnant women and their partners, will be assessed by the PDSS. We developed the PDSS, which is based on the Social Phobia Belief Scale (SPBS) [62], for this study in order to describe catastrophic beliefs about childbirth and future-related events that are eliciting fear (maximum of 3 beliefs). The PDSS assesses the probability of actual occurrence of those catastrophic events, the severity, and the ability to cope with them in the future on the Visual Analogue Scale (VAS) [63], (0–100 %). And third, to assess responses to anxiety and fear in pregnant women we will administer the experimental PAFS based on the Dimensional Anxiety Self-report of Social Phobia level 3 DSM-IV [64].

Subsequently, three instruments will be included to assess labour pain. First, anticipated and experienced cognitive and emotional components of labour pain will be assessed by the 13 item self-report Catastrophizing Labour Pain (CLP) subscale derived from the Labour Pain Cognitions and Coping List (LPCCL) [65], the 20 item self-report Labour Pain Acceptance Questionnaire (LPAQ), ([name], [name], [name], [name], [name]: LPAQ, unpublished), an adaptation of the Chronic Pain Acceptance Questionnaire (CPAQ) [66], and the expected and experienced severity of labour pain will be assessed by the VAS [63] (0–10).

Last, the willingness to accept obstetrical interventions without medical indications will be assessed by the Dutch version of the Willingness to Accept Obstetrical Interventions measure (WAIO) [67], ([name], [name], [name], [name]: Dutch version of WAIO, unpublished).

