### Sample size

Assuming a medium effect size of MBCP compared to the comparison condition and referrals of 30 % from primary to secondary midwifery care due to maladaptation to childbirth [28] we aim to include *n* =128 pregnant women with a high level of FoC and their partners (64 couples in each arm) to achieve a power of 80 % to find a significant effect (test of between-within interaction, 5 % alpha, 0.5 correlation). We based our power calculations on a medium effect size versus the large effect size found in a single-group trial of MBCP for decreasing pregnancy anxiety (*d* = 0.81, *p* < 0.0001) in the study of Duncan and [name] [40] and the overall medium mean effect size of MBP’s (*d* = 0.59) [55], in part due to the unknown effect size of the FoCC comparison condition.

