### Statistical analyses

#### Primary analyses

Dichotomous outcome data will be analysed using Chi-square tests or logistic regression using the method of ‘last observation carried forward’ (i.e., assuming no change) to handle dichotomous incomplete data. Continuous outcome data will be analysed with Multi-level analyses. Multi-level analyses with full information maximum likelihood (FIML) estimation use all available data and allow intention-to-treat analyses including all participants with incomplete data and participants who dropped out during the study. Continuous variables will be transformed into *Z*-scores. In this way, the parameter estimates can be interpreted as a measure of effect: i.e., as Cohen’s *d* for dichotomous predictors and as *r* for continuous predictors. Outliers will be identified. Analyses will be run twice: once in which all original scores will be included and once in which outliers will be changed to *Z*-scores (-) 3.29. Dependent variables will be level of FoC, labour pain and willingness to accept obstetrical interventions without medical indications. Predictors will be the different time measurements (T2, T3, and T4 against T1) and condition (MBCP versus FoCC). Interaction effects of time X condition will be added to the model to examine which programme is more effective over time.

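### Three unranked primary outcomes on seven instruments, no lead test named, and a sample size that provides for only one test at 5%

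*Protocol article*

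**What the plan says.** All places are in the protocol article.

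- **Primary outcome measures** lists the outcomes: "Primary outcome measures are (a) FoC, (b) labour pain, and (c) willingness to accept obstetrical interventions without medical indications". On fear of childbirth (FoC) it says "The complexity of FoC will be measured by three instruments": W-DEQ-A/B, PDSS and PAFS. On pain, "three instruments will be included to assess labour pain": CLP, LPAQ and a VAS. Finally, "the willingness to accept obstetrical interventions without medical indications will be assessed by the Dutch version" of one further measure (WAOI). That makes seven instruments in three domains, with no order of importance.
- **Outcome measures, Table 4** gives the occasions. W-DEQ-A is taken at T1 and T2. W-DEQ-B ("Experienced fear of childbirth") is taken at T3 and T4. PDSS and PAFS ("Responses to anxiety and fear") are taken at all four occasions, CLP, LPAQ and WAOI at T1 and T2, and the pain VAS at T1 to T3.
- **Primary analyses** enters T2, T3 and T4 against T1, condition, and their interaction. It adds: "Analyses will be run twice: once in which all original scores will be included", and a second time with outliers recoded. It does not say which run decides.
- **Sample size** gives 128 women (64 couples per arm), 80% power, 5% alpha and a correlation of 0.5 for a "test of between-within interaction".

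**The concern.** The only significance level in the article belongs to the sample size calculation, which describes one test. The primary analysis offers several, all of equal standing. As written, any one of them could be reported as the primary result. A null W-DEQ finding could be set aside in favour of PDSS, which the article calls newly developed, or PAFS, which it calls experimental.

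Two things are at stake. The 5% would not be the chance that the trial makes a false primary claim. And if a correction is brought in later, the sample was not sized to bear it.

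**Working it through.** **1. Reproduce the sample size.** Inputs from Sample size: alpha 5%, power 80%, correlation 0.5, 64 per arm. Assumptions: medium means d = 0.5 (the article gives no number) and the test is two-sided (not stated).

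- SD of a change score, in baseline SDs: √(2(1 − 0.5)) = 1. The interaction test is then a two-sample comparison at d = 0.5.
- n per arm = 2(1.960 + 0.842)² / 0.5² = 62.8, so 63. The t-test version gives 63.77, so 64.
- Power at 64 per arm: 80.7% (normal) or 80.1% (t).

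The variants tried do not give 128. A one-sided test needs 50 per arm. A repeated-measures F test with f = 0.25 needs 34, 28 or 24 in total for 2, 3 or 4 occasions. Inflating by the 30% referral figure gives 128 / 0.7 = 183. Only one two-sided test at an unsplit 5% matches.

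**2. Count the primary tests.**

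- One per outcome domain: 3.
- One joint interaction test per instrument: 7.
- Every post-baseline cell in Table 4: W-DEQ 3 + PDSS 3 + PAFS 3 + CLP 1 + LPAQ 1 + VAS 2 + WAOI 1 = 14.
- The same without W-DEQ-B at T3 and T4, since version B has no T1 value: 14 − 2 = 12.

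**3. Chance of at least one false positive at 5% per test.** Under independence this is 1 − 0.95^k. The correlated columns come from simulating k equally correlated two-sided z tests (400,000 draws). The article gives no correlations between outcomes, so these values are assumptions.

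| Tests (k) | Independent | r = 0.3 | r = 0.5 | r = 0.7 | r = 0.9 |
|---|---|---|---|---|---|
| 3 | 14.3% | 13.7% | 12.6% | 10.9% | 8.3% |
| 7 | 30.2% | 27.1% | 23.0% | 17.8% | 11.5% |
| 12 | 46.0% | 39.8% | 31.9% | 23.2% | 13.5% |
| 14 | 51.2% | 43.8% | 35.0% | 24.9% | 14.1% |

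These figures count false positives in either direction.

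**4. What a later correction would cost.** Bonferroni as an illustration, at d = 0.5 with 64 per arm:

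| Tests | Alpha per test | Power | n per arm for 80% |
|---|---|---|---|
| 3 | 0.05/3 = 0.0167 | 65.6% | 86 |
| 7 | 0.05/7 = 0.00714 | 53.9% | 102 |
| 14 | 0.05/14 = 0.00357 | 44.7% | 115 |

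**The case against.** **Multiplicity procedures are commonly left to the statistical analysis plan, which is not shown.** This stands in part. The article does not say that tests go uncorrected; it states no correction. But choosing the primary outcomes and sizing the trial on them are protocol decisions. Both are made here and they do not match. A later correction could control the error rate, but it would not restore the power in step 4.

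**Fourteen is not a minimum.** This stands. The article does not say whether the interactions are judged jointly or one contrast at a time, and the W-DEQ-B contrasts require experienced fear to be treated as the same measure as anticipated fear. Counts above 14 are possible, because PDSS has three ratings, but the article does not say how they are scored or analysed. The supportable range is 3 to 14 or more.

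**The tests are correlated.** This stands. They share participants, a baseline and overlapping constructs, so the independence figures are upper values.

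**A reader might double the count to 28 because each analysis is run twice.** The article does not support that. The second run changes only outliers and largely repeats the first. The defect is that neither run is named as decisive.

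**A reader might also treat all the newer scales as experimental or unvalidated.** The article uses the word experimental only for PAFS. LPAQ is described as an unpublished adaptation of an existing questionnaire, and the Dutch WAOI is unpublished too. The point rests on the missing ranking, not on the quality of the scales.

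**The Aims section hypothesises benefit on all outcomes.** If every one had to succeed, alpha would not inflate, but power for joint success would fall below 80%. No such rule is stated.

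**Conclusion.** The point holds. The article defines no lead primary test and no success rule, and its sample size provides for one test at an unsplit 5%. That last statement rests on reading medium as d = 0.5 and the test as two-sided.

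If each primary test is judged at 5%, the chance of at least one false positive exceeds 5% on every reading examined. It runs from about 8% (3 tests, correlation 0.9) to 51% (14 independent tests).

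A reader might take 51% as the trial's actual false-claim rate. It is the top of the range, and it needs both the per-contrast count and independence. Nor do the documents show that no correction will ever be applied; they show that none is stated and none was allowed for in the sample size.

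**What to change.** By a dated amendment made before outcome data are examined:

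1. Name one lead confirmatory test. One candidate is the T2-versus-T1 time-by-condition contrast for W-DEQ-A, on original scores, at two-sided 5%. W-DEQ-A is the entry-criterion measure and is taken at both occasions. This keeps the model already described under Primary analyses.
2. If that test succeeds, test one named labour-pain instrument and WAOI, either in a fixed order or by Holm across those two.
3. Make the remaining instruments and the T3 and T4 contrasts secondary.
4. Label the outlier-recoded run a sensitivity analysis.

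The amendment changes wording only: no added participants and no dropped measurements. Recruitment began in April 2014 and the trial is registered, so the change has to be dated and visible.

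There are real downsides. The other instruments no longer carry a confirmatory claim. Nor do the postpartum time points, although the Aims section covers the periods after labour and during maternity leave and hypothesises longer lasting effects. Planned power is kept only for the first test; the later ones are reached only if it succeeds. If the postpartum effect matters more to the investigators, they could choose a different lead test, but they should still name one.

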Sleep quality will be assessed by the Pittsburgh Sleep Quality Index (PSQI) [74] with additional sleep efficiency questions, and the Insomnia scale derived from the Holland Sleep Disorders Questionnaire (HSDQ-I) [75]. Sleep quality of the infant will be measured by the Dutch version of the Infant Sleep Vignettes Interpretation Scale (ISVIS) [76], ([name], [name], [name], [name]: Dutch version of ISVIS, unpublished) [76], and by the Brief Infant Sleep Questionnaire (BISQ) [77]. Furthermore, fatigue will be assessed by the Multidimensional Assessment of Fatigue (MAF) [78]. Satisfaction with childbirth will be assessed by the Dutch version of the Salomon’s Item List (SIL) [79]﻿, (﻿﻿﻿[name], [name], [name], [name]: Dutch version of SIL, unpublished﻿﻿). Birth outcome for mother (e.g., modus partus) and infant (e.g., birth weight and APGAR score) will be derived from the medical report (MR). And last, breastfeeding self-efficacy of the mother will be assessed by the Dutch version of the Breastfeeding Self-Efficacy Scale-Short Form (BSES-SF) [80]﻿, ([name], [name], [name], [name]: Dutch version of BSES-SF, unpublished﻿).

